## Objectives and Hypotheses

The APPLES study is a population-based, prospective controlled study enrolling at minimum of 500 patients and designed to assess the impact of extended wait-times for bariatric care and examine the clinical and cost-effectiveness of bariatric treatment in the Canadian context.

The three major objectives of APPLES are:

1. To assess the impact of extended wait times for bariatric care by examining the two-year change in clinical, economic and humanistic outcomes in wait-listed patients. We hypothesize that patients will report progressive deterioration in these outcomes over time.

2. To determine the clinical effectiveness and changes in health-related quality of life associated with modern bariatric procedures and compare these outcomes to medically treated controls and untreated wait-listed controls. We hypothesize that surgery will markedly reduce body weight, decrease the need for unplanned medical care, and increase quality of life compared to controls.

3. To compare the costs associated with bariatric surgery to costs associated with medical and wait-listed controls over three years, from societal, public payor, and health care payor perspectives. We hypothesize that lower indirect, out of pocket and productivity costs will offset increased direct health-care costs resulting in lower total costs for bariatric surgery.

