### Follow-up

Follow-up visits will be scheduled every 6 months for two years and will be performed in-person or by telephone if necessary. The final two year follow-up visit will be performed in-person.

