### Statistical Analysis and Sample Size Considerations

#### Clinical, Humanistic and Economic Outcomes in Wait-listed Patients

This analysis specifically focuses on the wait-listed group and will examine two-year change scores in each relevant outcome using the appropriate statistical methodology. Analyses will be conducted in all wait-listed patients as well as those indicating a specific interest in surgery. Examples of clinical outcomes include anthropometric indices, blood pressure, lipid profile, glycemic control, diabetes prevalence. Examples of humanistic outcomes include QOL and patient satisfaction. Economic outcomes include total and categorical costs. For example, two-year change scores will be analysed for QOL domains (e.g. SF-12, IWQoL-Lite) using appropriately calibrated and constructed linear regression models and/or analysis of variance. Because these are self-reported data collected on a semi-annual basis, we will use a "last-value carried forward" approach to handle missing data as our primary analytic strategy.

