##### Sample Size Considerations

The sample size of 150 subjects provides ample power to detect 2-year change scores and explore potential independent correlates of change. For example, for a 2-year change in SF-12 domains such as physical function, with baseline score of 31.6, SD 9,[61] a clinically important change in QOL of 5 points, two-sided alpha = 0.05, beta = 0.90, and a 30% attrition rate, 48 patients would be required. Similarly, to detect a 2-year change in IWQoL-Lite, with a baseline score of 28.7, SD 18.7,[61] a clinically important change in QOL of 10 points,[62] two-sided alpha = 0.05, beta = 0.90, and a 30% attrition rate, 51 patients would be required.

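### Carrying the last value forward as the primary strategy for six-monthly self-reported scores in wait-listed patients shrinks the two-year decline that objective 1 hypothesises, and its interval under-covers

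*Protocol article*

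**What the plan says.** All references are to the protocol article.

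- **Hypothesis.** Objective 1, under Objectives and Hypotheses, concerns two-year change in wait-listed patients: "We hypothesize that patients will report progressive deterioration in these outcomes over time".
- **Analysis.** Under Clinical, Humanistic and Economic Outcomes in Wait-listed Patients, the worked example is that "two-year change scores will be analysed for QOL domains (e.g. SF-12, IWQoL-Lite") by linear regression and/or analysis of variance.
- **Missing data.** The same paragraph names a last-value-carried-forward "approach to handle missing data as our primary analytic strategy". The only reason given is "Because these are self-reported data collected on a semi-annual basis".
- **Schedule.** Under Follow-up: "Follow-up visits will be scheduled every 6 months for two years", in person or by telephone if necessary, with the two-year visit in person.
- **Attrition.** The Sample Size Considerations for this group use "two-sided alpha = 0.05, beta = 0.90, and a 30% attrition rate".

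The article names no other missing-data analysis for these outcomes.

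**The concern.** LOCF sets every change after the last contact to zero. Objective 1 expects the opposite, a steady worsening over the two years. If the hypothesis is true, a patient lost at month 6 contributes only the first part of the decline, and one lost straight after baseline contributes none. The method therefore assumes away part of what the objective sets out to measure. It also counts carried scores as real month-24 observations, so the standard error does not reflect the missing information.

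The stated reason does not support the choice. Neither self-report nor six-monthly collection makes scores stay constant after a patient is lost. Up to five scores per patient are what a repeated-measures model or multiple imputation can use.

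At stake is the reported size of the harm of waiting on quality of life. The Discussion says such findings may inform triage and the allocation of surgery, so size matters as well as significance.

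**Working it through.** **Inputs from the article.** 150 wait-listed patients; 30% attrition; visits at 0, 6, 12, 18 and 24 months. SF-12: SD 9, important change 5 points ("with baseline score of 31.6, SD 9,[61] a clinically important change in QOL of 5 points"). IWQOL-Lite: SD 18.7, important change 10 points. Two-sided alpha 0.05; the stated beta of 0.90 is read as power 0.90.

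**Reproducing the plan's own figures (48 and 51).** For a one-sample test of change, n = (SD × (1.960 + 1.282) / change)².
- SF-12: 34.04. The exact t-based n is 37, and 37 × 1.3 = 48.1.
- IWQOL-Lite: 36.74. The exact t-based n is 39, and 39 × 1.3 = 50.7.

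Both stated figures are reproduced, so the quoted SD is in effect being used as the SD of change.

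**Share of the true change that LOCF keeps.** Assume linear worsening and loss unrelated to trajectory. With attrition d and last visit at month t, share kept = (1 − d) + d × mean(t/24).

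| Last visit of those lost | Share kept at d = 0.30 | SF-12 (true 5) | IWQOL-Lite (true 10) |
|---|---|---|---|
| Even over 0, 6, 12, 18 months | 0.70 + 0.30 × 0.375 = 0.8125 | 4.06 | 8.12 |
| All at baseline | 0.70 | 3.50 | 7.00 |
| All at month 18 | 0.70 + 0.30 × 0.75 = 0.925 | 4.62 | 9.25 |

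The shrinkage is 18.75% with even losses and runs from 7.5% to 30%. At 10% attrition, 90% to 97.5% of the change is kept. Timing of loss is not given in the article, hence the range.

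**Coverage of the nominal 95% interval, 150 patients, true SF-12 decline of 5 (simulation).**
- Equal correlation of 0.5 between visits: 76% with even losses, 36–38% with all losses after baseline, 92% with all losses after month 18.
- Same model with even losses: 80% at correlation 0.3 and 62% at 0.7.
- Variance of change split equally between patient slopes and noise: 72% with even losses and 37% with all losses after baseline. For IWQOL-Lite these are 74% and 39%.

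**Hand check.** With SD 9 the standard error is 9/√150 = 0.735. Even losses give a bias of 5 − 4.0625 = 0.9375, or 1.28 standard errors. With a t quantile of 1.976, coverage is about Φ(1.976 − 1.276) = 76%. Loss after month 18 gives a bias of 0.375, or 0.51 standard errors, and coverage of about 92%.

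**Carried values counted as data.** If all losses follow baseline, 30% of patients carry a change of exactly zero. The variance becomes 0.7 × 81 + 0.7 × 0.3 × 25 = 61.95, so SD = 7.87 and the standard error is 7.87/√150 = 0.643. The 105 patients actually observed at month 24 support 9/√105 = 0.878. A bias of 1.5 is then 2.33 standard errors, and coverage is about 36%, in line with the simulation.

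**Power.** In the simulations with 150 patients, power to reject zero change stayed near 100%.

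**Loss that depends on trajectory** (SF-12, true change −5.0; patient slopes with SD 9 × √0.5; last visits spread evenly).
- The fastest-declining 30% are lost: LOCF −2.7, completers −1.9.
- The best-faring 30% are lost: LOCF −5.4, completers −8.1.

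LOCF can therefore err by more than in the table, or in the other direction, and in both cases completers alone do worse.

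**The case against.** **Direction is not certain.** Deterioration is a hypothesis under test. A reader might infer that LOCF must always understate the harm of waiting. The documents do not support that: it holds if patients decline as hypothesised and loss is unrelated to trajectory, and the last calculation shows it can reverse. This objection stands, and the claim is conditional.

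**The size rests on assumptions.** Linearity, correlation and timing of loss are not in the article, and 30% is a sample-size allowance, not a forecast. Telephone follow-up may limit missing interim scores. This also stands, which is why ranges are given. At the mild end the effect is small: an estimate of 4.6 with 92% coverage.

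**It does not reach all of objective 1.** A reader might take the whole of objective 1 as compromised. The rationale given for LOCF refers to self-reported, semi-annual data. Body weight, blood pressure and cardiovascular risk factors are remeasured at two years, and part of the cost data comes from administrative linkage. The calculation does not apply to those.

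**Patients entering the clinic.** A reader might infer that wait-listed patients who enter the clinic are frozen at their last waiting score. The censoring rule for patients who cross over is written for the comparison of surgery with medical and wait-listed controls. The section on wait-listed patients states no such rule.

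**The bias is conservative and power is ample.** Where it runs as described, it works against the study's own hypothesis and would not manufacture evidence of harm. That is correct, and it lowers the severity. It does not excuse a biased estimate and a short interval when the purpose is to measure impact.

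**Other analyses may exist.** Naming a primary strategy leaves room for secondary ones that a condensed article need not list. But the primary choice itself is fixed in the text and is the point at issue.

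**Conclusion.** The point holds in conditional form, for the six-monthly self-reported outcomes in wait-listed patients. If decline is linear and loss is unrelated to trajectory, 30% attrition spread evenly over visits shrinks the estimated two-year change by about 19%. A true decline equal to the plan's own important change is then reported below it: SF-12 about 4.1 instead of 5 (3.5 to 4.6 by timing of loss). Coverage of the nominal 95% interval falls to roughly 72–76%, or about 37% to 92% by timing, under assumed covariance structures. If loss depends on trajectory, the bias can be larger or reverse. The harm is to the size of the estimate and its interval, and not to the power to reject zero change. This should be fixed, but it does not undermine the study.

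**What to change.** For SF-12, IWQOL-Lite and the other six-monthly self-reported scores in wait-listed patients:

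1. Make the primary analysis a mixed model for repeated measures on all available 0, 6, 12, 18 and 24 month scores, with visit as a factor and an unstructured covariance. The estimate is the change at month 24.
2. For non-normal outcomes, use multiple imputation based on all available scores.
3. Add a missing-not-at-random sensitivity analysis that shifts the unobserved scores by a range of deltas. The primary model assumes that loss is explained by the observed data, and the trajectory-dependent results above show why that needs testing.
4. Keep LOCF only as a sensitivity analysis, and do not replace it with a completers-only analysis.

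The cost is analysis wording and programming. The scores are already scheduled every six months, so no extra patients, visits or data are needed.

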##### Sample Size Considerations

The sample size of 150 subjects provides ample power to detect 2-year change scores and explore potential independent correlates of change. For example, for a 2-year change in SF-12 domains such as physical function, with baseline score of 31.6, SD 9,[61] a clinically important change in QOL of 5 points, two-sided alpha = 0.05, beta = 0.90, and a 30% attrition rate, 48 patients would be required. Similarly, to detect a 2-year change in IWQoL-Lite, with a baseline score of 28.7, SD 18.7,[61] a clinically important change in QOL of 10 points,[62] two-sided alpha = 0.05, beta = 0.90, and a 30% attrition rate, 51 patients would be required.

#### Comparing Clinical and Humanistic Outcomes in Patients Treated with Surgery to Medically Treated and Wait-listed Patients

Outcomes are similar to those listed above. Two-year mean changes in continuous variables will be compared between the surgical arm and medical or wait-listed controls using unpaired t-tests for continuous outcomes and chi-squared tests for dichotomous ones. Multivariable predictors of the 2-year change in a given outcome will be identified using appropriately constructed and calibrated covariate-adjusted linear regression models for continuous outcomes or logistic regression models for dichotomous ones. Patients who cross over to another study arm (e.g., medically treated patients who undergo surgery) will be censored at the point of cross over and a last-observation-carried-forward approach to missing data will be used for the primary analysis.

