### Outcomes Associated with Bariatric Surgery

Although no large scale, contemporary randomized controlled trials (RCTs) have examined the impact of surgery on cardiovascular morbidity or overall mortality, compelling data are available from high quality observational studies such as the Swedish Obesity Study (SOS), a matched cohort study of 2010 surgical and 2037 controls [16,17]. Compared to the poor long-term results of non-surgical therapy, surgery is the only therapy associated with substantial improvements in weight (averaging 33% after 2-3 years[18] and 16% after 10 years[16]); 15-year mortality rates (5.0% versus 6.3% in well-matched controls; HR 0.71; 95% CI 0.54 to 0.92);[19] 11-year incidence rates of first time cancers (HR 0.67; 95% CI 0.53-0.85);[17] and 7-year mortality rates from coronary artery disease (HR 0.41; 95% CI 0.21-0.78) and cancer (HR 0.40; 95% CI 25-0.65) [20]. In terms of other medical comorbidity, surgery increased remission rates for type 2 diabetes (73% versus 13%; p < 0.001; OR 5.5; 95% CI 2.2-14) in a 60-patient RCT;[21] and meta-analyses of primarily observational data has demonstrated that surgery is associated with resolution or improvement of type 2 diabetes, hypertension, dyslipidemia and sleep apnea in 70-86% of cases [18]. Additional studies demonstrate that surgery significantly (p < 0.05) improves psychosocial functioning,[22] quality of life,[23] and physical function [24].

In terms of Canadian data, a retrospective analysis of 1035 bariatric surgery patients from a single practice in Quebec reported 5-year excess weight losses of 61-75% following gastric bypass and banding [25]. In an earlier study, patients from this bariatric program (n = 1035) were also retrospectively compared with 5746 age and sex-matched controls identified using administrative data claims in Quebec (clinical variables such as height and weight were not available for controls) [26]. Mortality rates over 5 years were markedly lower in the bariatric surgery cohort compared to controls (0.68% versus 6.17%; RR 0.11, 95% CI 0.04-0.27) although the design of this study cannot rule out the very real likelihood that surgical selection bias (i.e., healthier and higher socioeconomic status patients with lower likelihood of surgical complications more likely to receive surgery) explains some if not most of these findings.

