## Methods/design

### Overall Study Design

In this prospective cohort study, consecutive and consenting patients enrolled in the Weight Wise Regional Obesity Program and without a contraindication to surgery will be enrolled. The minimum enrolment sample size will include 150 surgical patients, 200 patients receiving intensive medical therapy and 150 patients wait-listed to enter the clinic (Figure 1). The number of patients enrolled in the medical arm is larger because we anticipate an increased rate of censoring in this study arm, as some of these patients will ultimately undergo bariatric surgery within the two-year follow-up period.

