### Eligibility For Surgery

Within the adult specialty clinic, patients receive approximately 24-36 weeks of intensive lifestyle counselling (diet, exercise, behavioural modification), delivered by a multidisciplinary staff (internists, dieticians, nurses, physiotherapists, and psychologists) according to current recommendations [14]. Patients are seen approximately every 4-8 weeks. Patients interested in bariatric surgery are also evaluated for this procedure by the same multidisciplinary staff. Patients deemed to be appropriate candidates are subsequently evaluated by a bariatric surgeon. Patients with BMI levels ≥ 35-39.9 kg/m^2 ^and a major medical comorbidity (e.g., hypertension, type 2 diabetes, sleep apnea) or BMI levels ≥ 40 kg/m^2 ^are considered potential candidates for surgery. Absolute contraindications to surgery include pregnancy, uncontrolled psychiatric disease, active substance abuse or smoking (patients are required to quit prior to surgery), an active eating disorder (anorexia or bulimia), and high-risk for surgery medical status (e.g. severe coronary artery disease). Because of limited data documenting the benefits of surgery in patients younger than 18 years of age and evidence for possible harm in patients over 60,[47] procedures are not performed in these age groups. In order to access surgery, patients are also required to demonstrate commitment to attend scheduled appointments and adhere to lifestyle modification and behavioural therapy.

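### The surgery-versus-control comparison for Objective 2 is specified as unadjusted tests in a non-randomised cohort; the adjusted study-arm contrast should be named as the main estimate, as it already is for costs

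*Protocol article*

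**What the plan says.** Under Overall Study Design, the protocol article describes a cohort formed by the care patients receive: "The minimum enrolment sample size will include 150 surgical patients, 200 patients receiving intensive medical therapy and 150 patients wait-listed to enter the clinic". Objective 2 (Objectives and Hypotheses) is a treatment-effect question, with hypotheses that surgery lowers weight, reduces unplanned care and improves quality of life relative to controls.

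The analysis section for that objective states: "Two-year mean changes in continuous variables will be compared between the surgical arm and medical or wait-listed controls using unpaired t-tests". Chi-squared tests are named for dichotomous outcomes. The next sentence turns to regression: "Multivariable predictors of the 2-year change in a given outcome will be identified", by covariate-adjusted linear or logistic models. It does not say that study arm is a term in those models or that they supply the surgery-versus-control estimate.

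The cost section is worded differently. It labels its first step (ANOVA) as unadjusted, then plans covariate-controlled regression to obtain the independent association of surgery against medical or wait-list controls.

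On selection, Eligibility For Surgery says: "In order to access surgery, patients are also required to demonstrate commitment to attend scheduled appointments and adhere to lifestyle modification and behavioural therapy". The background section on surgical outcomes says of an earlier Quebec cohort that "the design of this study cannot rule out the very real likelihood that surgical selection bias" accounts for much of its apparent benefit, the mechanism being "healthier and higher socioeconomic status patients with lower likelihood of surgical complications more likely to receive surgery".

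**The concern.** In a non-randomised cohort, an unpaired t-test or chi-squared test compares the arms as they stand, and any baseline difference that predicts the 2-year change enters the estimate. Surgical patients have completed a clinic programme, shown adherence, been accepted by a surgeon and chosen an operation. Wait-listed patients have not yet entered the clinic, and medically treated patients include those who did not want surgery or were not accepted for it. Income and employment may differ as well.

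The article criticises an earlier cohort for this kind of selection and plans for it in the cost analysis. For clinical and humanistic outcomes it names only unadjusted tests for the arm comparison. If those tests carried Objective 2, part of a difference in quality of life or unplanned care could be patient selection, and the p-values would not hold their nominal error rate. The results are intended to inform how scarce surgical capacity is allocated.

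**Working it through.** **1. What the planned comparison assumes.** The article's one worked sample size for Objective 2 is for weight: difference 25 points, SD 17, two-sided alpha 0.05, power 90% (printed as a beta of 0.9), 30% attrition, 13 patients.

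- n per arm = 2 × [17 × (1.960 + 1.282) / 25]² = 9.72, rounded up to 10.
- 10 × 1.3 = 13. Dividing by 0.7 instead gives 15.

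The stated 13 therefore reproduces as a per-arm figure for an unadjusted two-sample comparison.

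**2. Inputs for the illustration.**

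- Arm sizes 150 surgical and 200 medical (Overall Study Design), with 30% attrition (Sample Size Considerations): 105 and 140 completers.
- SF-12 SD 9 and important change 5 points (Sample Size Considerations, wait-listed patients). The SD is attached to a baseline score; the SD of 2-year change is not given, so 9 is a proxy.
- Assumed, because the documents give no values: a baseline confounder differs between arms by δ SD and correlates r with the 2-year change. Three settings are shown.

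**3. Formulae.** Bias in SD units = δ × r. Standardised SE = √(1/105 + 1/140) = 0.1291. Shift in the test statistic, s = δ × r / 0.1291. Rejection rate with no true effect = 1 − Φ(1.96 − s) + Φ(−1.96 − s).

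**4. Results, surgery versus medical.**

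| δ | r | Bias (SD) | s | Type I error | Bias in SF-12 points (SD 9) | Share of 5 points |
|---|---|---|---|---|---|---|
| 0.2 | 0.3 | 0.06 | 0.46 | 7.5% | 0.54 | 11% |
| 0.3 | 0.4 | 0.12 | 0.93 | 15% | 1.08 | 22% |
| 0.5 | 0.5 | 0.25 | 1.94 | 49% | 2.25 | 45% |

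**5. Surgery versus wait-listed.** With 105 and 105 completers, SE = √(2/105) = 0.1380, and the same three biases give 7.2%, 14% and 44%.

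**6. If dropouts are retained.** The same section carries the last observation forward, so the analysed numbers could be nearer 150 and 200. Then SE = √(1/150 + 1/200) = 0.1080, and the rates for surgery versus medical rise to 8.6%, 20% and 64%. Using completers is the milder case.

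**7. Weight.** The planned difference is 25/17 = 1.47 SD. A bias of 0.12 SD is 2.04 points, about 8% of 25; a bias of 0.25 SD is 4.25 points, 17% of 25. Neither threatens the conclusion that surgery reduces weight.

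**The case against.** A reader might infer that confounding will simply be reported as a treatment effect. The text does not support that. The sentence after the t-tests plans covariate-adjusted regression on the same 2-year changes, under a heading about comparing surgery with controls. Study arm could well be a term in those models. The t-tests are never called primary; in that paragraph the word goes only with the rule for carrying observations forward. This stands, and it limits the point to which analysis is assigned to the arm contrast.

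A reader might also infer that control patients escaped the whole surgical screen. They did not. Every arm excludes patients with a contraindication to surgery, and Eligibility For Surgery counts active smoking, uncontrolled psychiatric disease and high medical risk among these. Patients expected to have difficulty attending visits are excluded too, and the age and BMI limits are common. This also stands. What remains different is demonstrated adherence, acceptance by a surgeon, preference for surgery and socioeconomic status.

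The error rates depend on imbalances and correlations that the documents do not give. That is correct, and they are shown only as a range.

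Finally, confounder lists and the choice of propensity method are commonly left to an analysis plan that is not shown, so their absence from the article is not held against it. The point rests on what the article does state: an unadjusted method for the arm comparison and a different stated purpose for the adjusted models.

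**Conclusion.** The point holds in a limited form. For Objective 2, the only method named for comparing surgery with controls is unadjusted, and the adjusted models are assigned to finding predictors. The cost section shows the fuller wording, and the article gives no reason for the difference.

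The weight conclusion is robust. The exposure lies in smaller effects: quality of life, unplanned care, satisfaction and risk factors. Under assumed biases of 0.06 to 0.25 SD and 105 versus 140 completers, type I error would be about 7.5% to 49%, and the bias on the SF-12 about 0.5 to 2.3 points against an important change of 5. These figures rest on the assumed confounder and on a baseline SD standing in for the SD of change. They show sensitivity and do not estimate the bias that will occur.

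**What to change.** State in the Objective 2 analysis section that the main estimate is the study-arm contrast (surgery versus medical, and surgery versus wait-listed) from a covariate-adjusted regression or propensity-weighted model, in line with the cost section. Fix the confounders in advance from baseline data collected in all arms: baseline value of the outcome, age, sex, BMI, comorbidities, smoking, income, employment and health care use in the year before enrolment. Do not select them by statistical significance. Keep the t-tests and chi-squared tests as descriptive.

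Leave interest in surgery out of the model: it is described only within the waiting-list questionnaire, which goes to wait-listed patients. Acknowledge residual confounding by adherence, which is not among the listed baseline data and which adjustment therefore cannot remove.

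The cost is analysis wording and programming; no new data are needed.

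### The methods stated for Objective 2 have no time-at-risk term, so a surgical versus medical comparison of unplanned care made under them would probably be biased against surgery

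*Protocol article*

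**What the plan says.** Objectives and Hypotheses (protocol article) lists three expected effects of surgery under Objective 2: lower weight, less unplanned care and better quality of life. On the last two it expects surgery to "decrease the need for unplanned medical care, and increase quality of life compared to controls".

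The analysis section for that objective is Comparing Clinical and Humanistic Outcomes in Patients Treated with Surgery to Medically Treated and Wait-listed Patients. It compares arms "using unpaired t-tests for continuous outcomes and chi-squared tests for dichotomous ones" and adjusts with "covariate-adjusted linear regression models for continuous outcomes or logistic regression models for dichotomous ones". Patients who change arm "will be censored at the point of cross over and a last-observation-carried-forward approach to missing data will be used for the primary analysis".

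Overall Study Design explains why the medical arm is larger (200 patients, against 150 in each other arm): "we anticipate an increased rate of censoring in this study arm", because some of its patients will have surgery within the two years.

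Data Collection and Outcome Measures obtains hospital encounters and emergency visits by linkage to provincial administrative data.

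**The concern.** Emergency visits and unplanned admissions accumulate with time observed. A medical patient censored at month 8 can contribute only 8 months of events. Carrying forward a cumulative count, or a status of no event so far, leaves that value where it stood at censoring, so LOCF amounts to truncation and does not restore the missing time. A t-test, a chi-squared test, or a linear or logistic model without an exposure term then sets this patient beside a surgical patient observed for the full two years.

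The protocol itself expects the shortfall to fall on one arm. At stake is one of the three effects named in the Objective 2 hypothesis: a real reduction with surgery could be hidden, and equal rates could look like an excess with surgery.

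**Working it through.** **The plan's own figure.** The protocol gives no event rate, crossover share or power statement for unplanned care. The one sample size in this part of the plan (13 patients, for weight) plays no part in the check.

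**Inputs from the document.** 150 surgical and 200 medical patients; two years of follow-up; more censoring expected in the medical arm.

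**Assumed inputs.** A share c of medical patients crosses over, uniformly over 0 to 2 years; surgical patients are followed for the full two years; events occur at a constant rate; crossover is unrelated to event risk. For the any-event figures and the simulation, the control rate is 0.5 events per patient-year.

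**Truncated counts.** Mean medical follow-up is 2 × (1 − c/2) years, so the apparent surgical/medical ratio is the true ratio divided by (1 − c/2).

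| c | Mean medical follow-up (years) | Apparent ratio, true ratio 1.00 | Apparent ratio, true ratio 0.70 |
|---|---|---|---|
| 15% | 1.85 | 1/0.925 = 1.08 | 0.76 |
| 30% | 1.70 | 1/0.85 = 1.18 | 0.82 |
| 40% | 1.60 | 1/0.80 = 1.25 | 0.88 |

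**Any event, c = 30%, equal rates.** Surgical: 1 − exp(−0.5 × 2) = 63%. A medical crossover, averaged over uniform censoring times, has 1 − 0.632 = 36.8%. Medical arm: 0.70 × 63.2% + 0.30 × 36.8% = 55%.

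**Simulated tests.** Poisson counts, 150 versus 200 patients, 4,000 replicates, two-sided 5% level:

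| c | False positives: t-test | Chi-squared | Person-time rate | Power at true ratio 0.70: t-test | Person-time rate |
|---|---|---|---|---|---|
| 15% | 11% | 12% | 5% | 63% | 84% |
| 30% | 29% | 32% | 5% | 33% | 83% |
| 40% | 46% | 50% | 5% | 16% | 82% |

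Without crossover, t-test power is 85%. The t-test false positives are almost all against surgery. With overdispersed counts (gamma-Poisson, dispersion 1, 3,000 replicates) at c = 30% and the same event rate, false-positive rates are lower: 17% for the t-test, 19% for chi-squared and 5% for a rate comparison. The size therefore depends on the event distribution as well as on c.

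**Informative crossover, c = 30%, crossovers with twice the event rate of other medical patients.** Count in units of the other medical patients' yearly rate. The truncated medical mean is 0.70 × 2 + 0.30 × 2 × 1 = 2.0, over a mean of 1.7 years, a rate of 1.18. What no effect means now matters:
- If the surgical rate equals that of patients who never cross over (1.0), the truncated ratio is 2.0/2.0 = 1.00 and the person-time ratio is 1.0/1.18 = 0.85. In simulation with crossovers at 2.5 times the rate, the truncated ratio falls to 0.94.
- If the surgical rate equals the whole medical arm's average (0.70 × 1 + 0.30 × 2 = 1.3), the truncated ratio is 2.6/2.0 = 1.30 and the person-time ratio is 1.3/1.18 = 1.11.

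Under the second benchmark the rate analysis is closer to the truth; under the first it is further away. In neither case does it remove informative crossover.

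**The case against.** The strongest reply is that the protocol never assigns these tests to unplanned care. The section says only "Outcomes are similar to those listed above", and the earlier list, given as examples, does not include unplanned care. Encounters and emergency visits appear under economic data, and a count model is a detail that a condensed article may leave to a fuller document. In the wait-list section, carrying values forward is justified by the data being self-reported every six months, which does not describe administrative records. Carrying forward per-interval counts would not have the truncating effect either.

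Much of this stands. That the tests apply to unplanned care is an inference, and the document does not say that a truncated count will be treated as a two-year total. But this is the only between-arm analysis section for Objective 2, it sorts outcomes only into continuous and dichotomous, and its crossover and LOCF rules carry no exception for linked data. The cost section's separate methods for cumulative costs do not extend to this hypothesis. The stated rules, followed as written, mishandle the outcome, which is more than a missing detail.

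It is also fair that a rate model does not cure selective crossover. Access to surgery depends on medical risk and demonstrated adherence (Eligibility For Surgery), although patients with contraindications are excluded from every arm.

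**Conclusion.** The point holds in conditional form. If unplanned care is analysed under the stated rules as a cumulative count or an any-event proportion, unequal follow-up would probably bias the surgical versus medical comparison against surgery. With an assumed 15% to 40% uniform crossover unrelated to risk, equal rates appear as a ratio of about 1.08 to 1.25. The false-positive and power figures rest further on the assumed event rate and dispersion.

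A reader might infer that the plan biases the whole comparison against surgery. The document does not support that. Extra censoring is stated only for the medical arm, so no direction is shown against wait-listed controls. Even against medical controls, the direction depends on crossover not being concentrated in patients with much higher event rates. Nor does the document fix a t-test on truncated counts of unplanned care; that remains an inference from the only methods offered.

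**What to change.** In the Comparing Clinical and Humanistic Outcomes section, state that emergency visits and unplanned hospitalisations are analysed as rates over observed person-time up to crossover, using the administrative linkage. An example is negative binomial regression with log observed time as offset and the baseline covariates, reported as adjusted rate ratios. State that LOCF does not apply to these counts.

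Add a sensitivity analysis for informative crossover, for example inverse-probability-of-censoring weights, or follow-up to two years by initial arm using the linked data. The latter compares initial arms whatever treatment follows, so it answers a different question and should be labelled accordingly.

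The cost is wording and modest analysis time, because the linkage already supplies the encounters. The downsides are small: results become rate ratios instead of mean differences, and the primary rate analysis assumes that crossover is uninformative given the covariates.
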